#### Exclusion criteria

(a) current or past schizophrenia or psychosis, bipolar disorder, or severe eating disorder, demanding close medical monitoring; (b) history of organic mental disease; (c) current risk of suicide or self-harm (HRSD [46] suicide item > 2); (d) current substance abuse disorder; (e) being currently in psychotherapy.

### Treatments

Patients will be enrolled either in a treatment of 16 50-min sessions or in a waiting list. The treatment will be SET, which is manualized time-limited psychodynamic therapy adapted for depression [99, 100]. The treatment includes the use of supportive techniques, such as affirmation and empathic validation, as well as more expressive techniques, such as interpretation, confrontation, and clarification (SET [99, 100]). Participants who were enrolled in the waiting list will receive treatment 16 weeks later.

### Therapists

The treatment will be provided by experienced therapists. Before starting to treat patients, therapists will receive intensive training on the SET manual [99, 100] and will treat a pilot case coded for adherence to ensure adequate levels of proficiency. Therapists will participate in weekly group supervision during the duration of the trial, making extensive use of videotaped sessions for feedback. An international expert in SET with more than 25 years of experience will be involved in and will accompany the process of supervision.

### Fidelity check

To ensure that therapists adhere to the manual and are competent in the technique, they will attend weekly supervisions in which videotaped sessions will be viewed to identify and analyze instances of deviation from the manual. In addition, each therapy session will be videotaped, and external evaluators will rate the therapists' adherence and competence. Adherence and competence in treatment will be evaluated using the Penn Adherence-Competence Scale (PACS [103]). PACS consists of three subscales: supportive component, expressive component, and general therapeutic behaviors. The raters will be supervised by an international expert on the use of the PACS, with vast experience in using the PACS in RCTs on SET. In cases of low adherence or insufficient competence, the therapist and the supervisor will be informed and relevant supervision tools will be deployed (e.g., [104, 105](.

#### Procedure and randomization (see Fig. 4)

**Fig. 4 Fig4:**
[figure not shown]
Study timeline: key assessment points and data measures of Study 2

##### Recruitment and pre-study phase

Recruitment will take place through advertisements offering free treatment. All participants meeting inclusion and exclusion criteria for Study 2 will first be enrolled in Study 1 to identify their synchrony signature and then be enrolled in Study 2 (see details above in the procedure section for Study 1).

##### Randomization

Patients who meet the eligibility criteria and agree to participate in the study will be randomly assigned to either treatment of 16 50-min sessions or to a waiting list. Randomization will be performed by an independent institution, not involved in the study. Applicants who have not met the inclusion criteria or have met the exclusion criteria and therefore are not eligible for the study, but request psychotherapy, will be referred to alternative care. All outcome evaluator interviews will be videotaped, and 30% of the tapes will be randomly assigned and rerated by independent raters.

##### Treatment phase

**Process and outcome measures.** During the active phase of treatment, the HRSD [46] and self-report questionnaires will be administered weekly. Participating patients will be asked to complete self-report measures assessing their symptoms (e.g., BDI-II[49]) before each session and self-report measures assessing treatment processes following each session. Levels of insight will be measured at baseline and at the end of the treatment (at week 16). Every fourth session during the course of treatment, patients will be asked to complete computerized tasks and to provide saliva samples. In addition, the MINI [47, 48] and SIDP [50] will be measured at weeks 8 and 16.

**Termination**. Patients who choose to withdraw from treatment before the end of the active treatment phase will receive a dropout questionnaire. Their therapists will also be asked to complete a dropout questionnaire [106].

#### Synchrony Interaction Paradigm (SIP)

After completion of the active phase of the treatment (16 weeks), the participants will undertake the SIPSynchrony Interaction Paradig [45] vis-à-vis the same figures they interacted with before the therapy, adhering to the protocol detailed in Study 1.

##### Follow-up

Assessments will be scheduled at 3, 6, 12, and 24 months after the end of the active phase. The follow-up assessment sessions will include HRSD [46], MINI [47, 48], and a battery of self-report questionnaires. At 6 and 12 months, the SIDP [50] will also be administered. To avoid bias, patients will be asked not to join other psychotherapeutic programs and not to change medication dosages.

### Measures

#### Treatment outcome

##### Main outcome

Severity of depressive symptoms, measured using the HRSD [46], will be the primary outcome measure of the trial. The HRSD is a 17-item measure administered by clinical interviewers. Depressive symptom severity is calculated by summing up all 17 items.

##### Secondary outcomes

**Symptoms measures.** Self-reported symptoms (i.e., Beck Depression Inventory [49]; Beck Anxiety Inventory [52]), Outcome Questionnaire [53], and quality of life (Quality of Life Enjoyment and Satisfaction [54]).

**Interpersonal measures**. Anxiety and avoidance attachment orientations (i.e., Experience in Close Relationships [55], and difficulties in interpersonal relationships (i.e., Interpersonal Problems Inventory [56]).

##### Therapeutic process measures

Working alliance (WAI [69]), therapeutic interventions (Multi-theoretical List of Therapeutic Interventions, MULTI [107]), psychological flexibility (Psychological Flexibility Questionnaire [108], expectation from treatment (Outcomes and Experiences Questionnaire [109], and insight measures will be assessed using the SUIP [51].

#### Overview of statistical analyses

Analyses will be conducted using multilevel nested models of observations nested within clients nested within therapists to account for the hierarchical structure of the data. All analyses will be conducted using the Proc Mixed procedure in SAS. All have been used extensively in our lab. To test whether in the absence of intervention, the trait-like signature is deterministic, we will test the percentage of variance explained in synchrony with the therapist from the trait-like signature identified using the procedure developed in our lab (see Study 1). To determine whether changes occur in the synchrony signature in the treatment vs. the control condition, we will use a model of time by condition (treatment vs. control conditions) predicting synchrony development over the course of treatment. To determine whether transformation in the trait-like synchrony signature is associated with strengthening of the alliance and improvement in mental health in the treatment condition, we will use two models of synchrony by condition (treatment vs. control conditions) predicting alliance and mental health, respectively, over the course of treatment. To test whether those with poorer trait-like synchrony benefit most from deviations toward a healthier pattern, we will test the between-levels interaction between the trait-like signature and changes in it by treatment condition (treatment vs. control conditions) in predicting changes in mental health.

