### Design

Study 2 investigates how deterministic the trait-like synchrony signature (as mapped in study 1) is in the absence of intervention, and whether changes in the signature are associated with changes in mental health as a result of intervention. The target relationships will be those with the therapist. All participants in Study 2 will have undergone the process described in Study 1 before starting their participation in Study 2. First, participants will be enrolled in a first session with a therapist. Second, participants will be allocated to a randomized control trial (RCT) and randomized to either a 16 weeks waiting list or supportive-expressive treatment (SET [99, 100]) with the therapist they met at the first session. To ensure balance across age, sex, family status, baseline 17-item HRSD [46], and personality disorders, a minimization algorithm will be used. At the end of treatment, the participants will again undertake the SIP [45]) vis-a-vis the same figures they interacted with before the therapy. At the end of the trial, participants who were randomized to the waiting list will be enrolled in treatment. The trial will follow the Standard Protocol Items: Recommendations for Interventional Trials (SPIRIT) checklist [101] requirements for an RCT [101] with a design that includes both treatment and waiting list conditions.

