#### Power analysis

The main analyses will focus on the main outcome measure (HRSD [46]).

To calculate the required sample size for the moderation models (based on the most complex model), we used an approach modeled on Monte Carlo simulations, estimated using the R code generated by the MLPowSim software package, applying 10,000 Monte Carlo simulations, which produces more accurate results for power estimates than other methods for relatively small sample sizes. The power calculation was based on effect sizes from our pilot data. Assuming alpha = 0.05 and 16 repeated measurements of the outcome variable (including missing data), the simulations indicated a required sample size of 78 participants to ensure a power of at least 0.80.

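### The Study 2 between-arm models put both arms in one therapist hierarchy; if fitted as a shared intercept, it leaves most SET-only therapist variance out of the arm contrast, chiefly time by condition

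*Protocol article*

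**What the plan says.** The Study 2 section on statistical analyses sets one structure for the whole study: "Analyses will be conducted using multilevel nested models of observations nested within clients nested within therapists to account for the hierarchical structure of the data". Within it, the arms are compared directly on synchrony: "we will use a model of time by condition (treatment vs. control conditions) predicting synchrony development over the course of treatment". The same section lists synchrony-by-condition models for alliance and mental health, and an interaction of the signature, change in it and condition. It names no therapist term that is specific to an arm or varies by condition.

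The Study 2 Design section gives the order of events. "First, participants will be enrolled in a first session with a therapist". Participants are then "randomized to either a 16 weeks waiting list or supportive-expressive treatment (SET [99, 100]) with the therapist they met at the first session". The Treatments section adds: "Participants who were enrolled in the waiting list will receive treatment 16 weeks later". Therapist is not among the balancing factors: "To ensure balance across age, sex, family status, baseline 17-item HRSD [46], and personality disorders, a minimization algorithm will be used".

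The Study 2 power section sizes the trial at 78 for power of at least 0.80 by simulation, on these terms: "Assuming alpha = 0.05 and 16 repeated measurements of the outcome variable (including missing data". It mentions participants and repeated measurements but does not say whether a therapist level was simulated.

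**The concern.** Because of the first session, every waiting-list participant can carry a therapist label, so a three-level model with a therapist intercept will run in both arms without complaint. Over the randomised 16 weeks, however, that label describes continuing contact in the SET arm only. The data are partially nested.

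A therapist intercept shared by both arms describes something that raises or lowers SET and waiting-list clients of the same therapist together. In the contrast between arms such a term largely cancels. If therapists differ in how their SET clients fare, that variance is real and enters the true sampling variance of the contrast, but the model's standard error does not carry it. In a time-by-condition model an intercept likewise fails to capture differences between therapists in slope.

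At stake are the error rate and the confidence interval of the arm comparison: differences between a handful of therapists could pass for an effect of treatment on how synchrony develops.

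**Working it through.** **Inputs from the documents.** N = 78, alpha 0.05, power at least 0.80 (Study 2, Power analysis); the nesting (Study 2, Overview of statistical analyses); first session before randomisation, then SET with that therapist or 16 weeks of waiting (Study 2, Design and Treatments).

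**Assumptions, because the documents give no figure.** 1:1 allocation (39 per arm), a two-sided test, K = 4 to 13 therapists, therapist ICC in the SET arm of 0 to 0.20, total variance 1 in each arm, one client-level score (a change or a slope) per person.

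**The plan's own figure.** N = 78 cannot be reproduced: no effect size, variance components or number of therapists are stated. For reference only, a plain two-arm comparison with 39 per arm and 80% power detects d = (1.96 + 0.842) × √(2/39) = 2.802 × 0.2265 = 0.634. This is not the plan's moderation model.

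**Formula.** With m = 39/K SET clients per therapist:

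- true SE = √((2 + (m − 1) × ICC)/39)
- SE when the therapist effect drops out = √(2/39) = 0.2265
- type I error ≈ 2 × (1 − Φ(1.96 × ratio of the second SE to the first))

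Example, K = 6, ICC 0.10: m = 6.5; true SE = √((2 + 5.5 × 0.10)/39) = √(2.55/39) = 0.2557; ratio = 0.2265/0.2557 = 0.886; type I error = 2 × (1 − Φ(1.736)) = 8.3%.

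Ratio and type I error from the formula:

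| ICC | K = 4 | K = 6 | K = 8 | K = 13 |
|---|---|---|---|---|
| 0.05 | 0.906, 7.6% | 0.938, 6.6% | 0.955, 6.1% | 0.976, 5.6% |
| 0.10 | 0.834, 10.2% | 0.886, 8.3% | 0.915, 7.3% | 0.953, 6.2% |
| 0.20 | 0.730, 15.2% | 0.803, 11.5% | 0.849, 9.6% | 0.913, 7.4% |

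**Simulation of the shared-intercept fit** (REML, therapist assigned before randomisation, no true arm effect, 1,500 runs per cell), type I error:

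| ICC | K = 4 | K = 6 | K = 8 | K = 13 |
|---|---|---|---|---|
| 0 | 5.1% | 4.2% | 5.5% | 6.0% |
| 0.05 | 6.7% | 7.0% | 6.3% | 7.0% |
| 0.10 | 10.1% | 9.3% | 8.3% | 6.8% |
| 0.20 | 16.0% | 13.8% | 9.2% | 9.1% |

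A separate simulation with 1,200 runs per cell and K = 6, 8, 12 gave 6.7, 5.4, 6.9% at ICC 0.05; 9.0, 9.0, 6.8% at 0.10; and 14.2, 10.9, 8.4% at 0.20. The Monte Carlo standard error near 5% is about 0.6 points (√(0.05 × 0.95/1,200) = 0.0063), so single cells should not be over-read. Uneven caseloads also push the true variance above the equal-caseload formula.

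The shared term protected no better than ignoring therapists: 10.1% against 10.0% at K = 4, ICC 0.10.

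**Time by condition.** A contrast of client slopes, from which a therapist intercept drops out, with 20,000 runs per cell over K = 4 to 13, gave 5.6-7.7% at ICC 0.05, 6.0-10.1% at 0.10 and 7.7-15.8% at 0.20.

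**Predictor by condition.** For a client-level predictor interacting with condition, under the same SET-only therapist effect and a shared intercept (K = 6, 8, 12; ICC 0.05-0.20; 1,000 runs per cell, Monte Carlo standard error about 0.7 points), rejection was 4.6-7.2%, against 5.3-13.1% for the plain condition test in the same setting.

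**After the change.** With the therapist effect in the SET arm only, the ratio of mean model SE to true SE was 0.96-1.05 and type I error 2.8-4.7% over ICC 0.05-0.20 and K = 4 to 13. In the separate simulation, with 76 degrees of freedom, it was 4.3-7.7%; the excess at few therapists is the reason for small-sample degrees of freedom.

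**Power, for the reference d = 0.634 only**, from Φ(0.634/true SE − 1.96): 0.72-0.78 at ICC 0.05, 0.65-0.76 at 0.10, 0.53-0.72 at 0.20, the lower end at K = 4 and the upper at K = 13.

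**The case against.** The best defence is that the article states levels of nesting, not a full random-effects specification. A therapist-by-condition or therapist-by-time-by-condition term is compatible with its sentence, and a condensed article commonly leaves that detail to the analysis plan. This stands, and it makes the point conditional on how the nesting is fitted. It does not remove the point: the stated structure treats both arms alike, and its most direct reading gives the contrast almost no protection.

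A reader might infer that waiting-list participants have no therapist, so that nesting them is simply wrong. The Design section does not support that. Each has met one therapist before randomisation, and a shared term handles properly any first-session effect common to both arms. Cancellation is also not exact, since therapist is not a minimisation factor.

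A reader might also infer that the standard errors are certain to be too small. That requires therapists to differ in SET; at ICC 0 nothing goes wrong, and at ICC 0.05 the excess is small.

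Nor does the problem extend equally to the mental-health models. Those listed test predictor-by-condition interactions, where the inflation found was slight.

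Finally, it is tempting to say that the power calculation left therapists out. The power section is silent on this, and silence in an article is not evidence of omission.

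**Conclusion.** The concern holds in a conditional form. After the shared first session, treatment-phase therapist variance can arise only in SET, yet one therapist hierarchy is stated for both arms. If it is fitted as a common intercept and therapists differ in SET, the standard error of a bare arm contrast is too small: by about 2% at the mild end (13 therapists, ICC 0.05; formula ratio 0.976) and about 27-31% at the severe end (4 therapists, ICC 0.20; formula ratio 0.730, simulated 0.69). Against a nominal 5%, type I error is then about 5-7%, 7-10% and 8-16% at ICC 0.05, 0.10 and 0.20.

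These sizes rest on assumed therapist numbers, ICC and allocation, and on one score per client rather than the full repeated-measures model. The scope is the between-arm terms over the randomised 16 weeks, chiefly time by condition; analyses within the SET arm are not in question. N = 78 is neither confirmed nor shown to be wrong. The change is worth making because it is cheap and recruitment had not started at the time of writing.

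**What to change.** In the Study 2 Overview of statistical analyses, state that in the between-arm models over the randomised 16 weeks the therapist variance may differ by arm. Either of two forms will do:

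- a therapist random effect on the SET indicator, on the intercept and, in time models, on the slope; in Proc Mixed this is a RANDOM statement on the SET dummy with therapist as subject;
- a random therapist-by-condition term, with its counterpart for time, which also keeps any first-session effect common to both arms.

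Use Kenward-Roger degrees of freedom in either case. Keep the common therapist nesting for the analysis of synchrony at the first session, where every participant does meet the therapist.

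In the Study 2 Power analysis, state whether the 0.80 power includes therapist clustering in the SET arm. If it does not, rerun the existing simulation with the planned number of therapists and a range of ICCs, and restate the power.

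The cost is a few sentences, a changed RANDOM statement and possibly one rerun of the simulation; no new data are needed. The downside is slightly wider confidence intervals for condition effects and possibly a lower restated power.

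### Study 2's synchrony-by-condition model for alliance has no control-arm alliance course, and the between-arm synchrony comparison works only with the SIP at baseline and week 16 in both arms

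*Protocol article*

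**What the plan says.** All places are in the Protocol article, Study 2, unless noted.

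- **Design.** On which relationship is studied: "The target relationships will be those with the therapist". On order: "First, participants will be enrolled in a first session with a therapist". Patients are then "randomized to either a 16 weeks waiting list or supportive-expressive treatment", the latter with the therapist they have just met.
- **Treatments.** Therapy is 16 sessions. The waiting list gets therapy 16 weeks later.
- **Treatment phase.** Patients complete "self-report measures assessing treatment processes following each session". The section on therapeutic process measures lists the Working Alliance Inventory (WAI) among these.
- **Overview of statistical analyses.** For change in the synchrony signature: "we will use a model of time by condition (treatment vs. control conditions) predicting synchrony development over the course of treatment". For alliance and mental health: "we will use two models of synchrony by condition (treatment vs. control conditions) predicting alliance and mental health, respectively, over the course of treatment". A further model predicts mental-health change from the signature, change in it, and condition.
- **Synchrony Interaction Paradigm (SIP).** Everyone has a baseline SIP through Study 1. On the repeat: "After completion of the active phase of the treatment (16 weeks), the participants will undertake the" SIP again, with the same partners. The Design section likewise places the repeat when treatment ends. Neither section says outright that waiting-list patients repeat it at week 16, and the timeline figure is not available in the text reviewed.

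**The concern.** A condition term needs data from both conditions over the period the model covers. Alliance with a therapist, and synchrony with a therapist, arise in sessions, and one arm has none between randomisation and week 16. The analysis section nevertheless writes both models with a treatment-versus-control term over the course of treatment.

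What is at stake is the meaning of the result. The randomised contrast is what would separate an effect of therapy on synchrony from practice, growing familiarity with the SIP partners, and regression to the mean. A term that is not estimable returns no contrast. A simpler specification of the alliance model can still return a number, but it would set an association within ongoing therapy against a cross-sectional association from a single pre-randomisation session. A reader could take that as a randomised difference.

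The between-arm synchrony comparison also depends on a week-16 SIP in the waiting list. If that assessment is missed, it cannot be recovered once those patients start therapy.

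**Working it through.** **The plan's own figure.** The Power analysis gives 78 participants for power of at least 0.80 from a simulation. Its pilot effects, variance components and allocation ratio are not stated, so 78 cannot be reproduced. For orientation only, a simple comparison of two means (assumed 1:1, two-sided 0.05, 80% power) needs n per arm = 2 × 7.85 / d²:

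- d = 0.64: 15.70 / 0.4096 = 38.3, so 39 per arm, 78 in total
- d = 0.4: 15.70 / 0.16 = 98.1, so 99 per arm, 198 in total
- d = 0.8: 15.70 / 0.64 = 24.5, so 25 per arm, 50 in total

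The point below does not depend on this figure.

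**Inputs for the estimability check.** From the documents: one therapist session before randomisation in both arms; 16 sessions in the therapy arm; no described therapist contact in the waiting list for 16 weeks; baseline SIP in everyone. Assumed: 39 per arm, and a therapy-arm schedule of the intake session plus 16. The ranks do not depend on these exact numbers.

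**Time by condition on synchrony.** Fixed-effect columns are 1, t, g and t×g, with g = 1 for therapy and g = 0 for the waiting list. All four coefficients are estimable only if the rank is 4.

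| Data entering the model | Rows | Rank |
|---|---|---|
| Therapist sessions: therapy arm t = 0 to 16, waiting list t = 0 only | 39×17 + 39 = 702 | 3 of 4 |
| SIP at 0 and 16 in both arms | 78×2 = 156 | 4 of 4 |
| SIP at 0 and 16 in the therapy arm, 0 only in the waiting list | 39×2 + 39 = 117 | 3 of 4 |

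In the first and third rows, t is non-zero only where g = 1, so t×g equals t in every row. The interaction is then indistinguishable from time. In the second row there are four distinct arm-by-time cells for four coefficients, and the interaction is identified from two occasions.

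A fourth possibility is that the waiting list repeats the SIP only after its own 16 weeks of therapy, at about 16 + 16 = 32 weeks. A model could then be fitted, but it would compare treated patients with patients treated later, and not with untreated controls.

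**Synchrony by condition on alliance.** Split synchrony s into the person mean s̄ and the deviation s − s̄. The columns are 1, g, s̄, s − s̄, g×s̄ and g×(s − s̄).

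- A waiting-list patient has at most one therapist observation, so s = s̄ and s − s̄ = 0.
- Hence g×(s − s̄) equals s − s̄ in every row. The rank is 5 of 6, and the within-person interaction is not estimable.
- Without the split (columns 1, g, s, g×s) the rank is 4 of 4. The waiting-list slope then rests only on differences between patients at one pre-randomisation session. It says nothing about strengthening of alliance.
- Replacing therapist synchrony with SIP change as the predictor does not help. The outcome in the waiting list still stops at one pre-randomisation value.

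**Models for mental health.** Their outcome, the HRSD, needs no therapy session. Their predictor, change in the signature, needs a SIP before and after in each arm, as in the second row of the table.

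**The case against.** The strongest reply concerns synchrony. The model's stated purpose is to detect change in the synchrony signature, which the SIP measures with several partners and without any therapy session. The Design section has participants repeat the SIP and only then says that waiting-list patients enter therapy. The SIP section marks the repeat at 16 weeks, which is also the length of the waiting list. The natural order is a week-16 SIP in both arms, and the missing timeline figure may show it. This stands. A reader might infer that every between-arm synchrony test is inestimable, or that the repeat SIP is scheduled after the waiting list's own therapy. The documents support neither. They leave open which synchrony measure and which occasions enter the model. Even so, two SIP occasions are not a development over the course of treatment, so the wording needs attention on either reading.

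A reader might also infer that the sample size of 78 is undermined, because it assumes 16 occasions that the waiting list lacks. The documents do not support this. The wording is "Assuming alpha = 0.05 and 16 repeated measurements of the outcome variable (including missing data"), and that section names the HRSD as the main outcome. How the simulation treated the synchrony predictor is not stated.

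On alliance, it can be said that the waiting list is not wholly without data, that the WAI is also given with SIP partners (Study 1, Measures), and that the stated aim concerns association in the treatment condition. One pre-randomisation rating is not a course, and alliance with a SIP partner is not the therapeutic alliance. The stated aim supports removing the condition term from this model.

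Finally, an article may leave detail to a fuller document. Here, however, the article itself fixes the condition term and the time frame, and these conflict with its own design.

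**Conclusion.** The point holds firmly for alliance and conditionally for synchrony.

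- **Alliance.** The waiting list has 0 therapist sessions between randomisation and week 16, against up to 16 in the therapy arm. The within-person synchrony-by-condition term is not estimable (rank 5 of 6), and the undecomposed version does not address strengthening of alliance.
- **Synchrony.** Time by condition is not estimable for session-level synchrony with the therapist (rank 3 of 4). It is estimable for the SIP signature if both arms repeat the SIP at week 16 (rank 4 of 4).
- **HRSD moderation models.** These are estimable on the same condition.

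This assumes that the waiting list has no therapist contact beyond the first session, since none is described. The randomised comparison of the HRSD, the primary outcome, is not affected. The change matters because it decides which of the trial's mechanism claims rest on randomisation.

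**What to change.** 1. Fit the models for therapist alliance and session-level synchrony in the treatment arm only, without a condition term, and report them as within-arm associations.
2. Define the between-arm synchrony outcome as the SIP-derived signature at baseline and week 16 in both arms. State that the waiting list's repeat SIP takes place at week 16, before their therapy starts.
3. Use that same SIP change as the synchrony-change predictor in the HRSD models.

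Optionally, check that the power simulation treats signature change as a person-level predictor.

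The cost is revised analysis wording and one sentence on the timing of an assessment the plan already includes. The trial registration entry says recruitment has not started, so both can be settled before any waiting-list patient reaches week 16. The downside is that the alliance result becomes a non-randomised association.

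### The between-arm comparison of synchrony change does not say that it uses the pre-randomisation SIP as a baseline adjustment; stating this is a free efficiency gain of about 5% to 35% in variance, most likely towards the lower end.

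*Protocol article*

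**What the plan says.** The statistical overview for Study 2 sets out the comparison of signature change between arms in one clause: "we will use a model of time by condition (treatment vs. control conditions) predicting synchrony development over the course of treatment". The general framework is "multilevel nested models of observations nested within clients nested within therapists to account for the hierarchical structure of the data", fitted in SAS Proc Mixed. The clause names no baseline covariate. It does not say whether a condition main effect is included, how time is coded, or which within-client covariance is used.

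The order of events is clear. The Study 2 Design section says: "All participants in Study 2 will have undergone the process described in Study 1 before starting their participation in Study 2". The recruitment section agrees that eligible people will "first be enrolled in Study 1 to identify their synchrony signature and then be enrolled in Study 2". A first session with the therapist follows, and only then allocation: "Second, participants will be allocated to a randomized control trial (RCT) and randomized to either a 16 weeks waiting list". The signature is measured again later: "At the end of treatment, the participants will again undertake the SIP". The later SIP section places this after the 16 weeks, with the same partners, "adhering to the protocol detailed in Study 1".

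Baseline synchrony is not among the balancing factors: "To ensure balance across age, sex, family status, baseline 17-item HRSD [46], and personality disorders, a minimization algorithm will be used".

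**The concern.** Because the first SIP comes before allocation, any difference between the arms in baseline synchrony is due to chance. A conventional time-by-condition model nevertheless estimates a separate baseline mean for each arm. With one measurement before and one after, its interaction is exactly the difference in mean change. A change score subtracts the whole of a chance baseline difference, although only a fraction r of it is expected to persist when the variances are equal. That adds noise which the data already collected could remove. Minimisation does not balance on baseline synchrony, so the design does not limit this chance difference directly.

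At stake is the precision of the comparison that tells whether the signature changes under therapy rather than over time alone. The Study 2 power section sizes the trial for moderation models with the HRSD as main outcome. It states no power for this synchrony contrast.

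**Working it through.** **The plan's own figure.** The Study 2 power section gives 78 participants for power of at least 0.80. It cannot be reproduced, because the pilot effect sizes, the variance components and the allocation ratio are not given. It also concerns a different analysis, so it does not bear on the contrast examined here.

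**Inputs.** From the article: baseline SIP before randomisation, one repeat SIP after 16 weeks, 78 participants, alpha 0.05. Assumed: 1:1 allocation (39 per arm), two-sided test, no attrition, equal variances at the two SIPs, one continuous synchrony score, no therapist clustering, and r from 0.3 to 0.9.

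**Why two occasions.** The Treatments section says that waiting-list participants start treatment 16 weeks later, so they have no therapy sessions in the comparison period. The SIP is the only signature measurement described as taken before allocation and repeated after 16 weeks.

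**Formulas.** With n per arm and variance σ²:

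- change-score contrast: (2σ²/n) × 2(1−r)
- baseline-adjusted or common-baseline contrast: (2σ²/n) × (1−r²)
- ratio: (1−r²) / [2(1−r)] = (1+r)/2
- reduction: 1 − (1+r)/2 = (1−r)/2

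The equal-variance assumption does not decide the direction. With standard deviations s0 and s1, the two variances are proportional to s0² + s1² − 2r·s0·s1 and s1²(1−r²). Their difference is (s0 − r·s1)², which is never negative.

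**Results.** The power columns use a two-sample t test with 39 per arm and an illustrative arm difference of 0.5 SD, standardised by √[2(1−r)] or √(1−r²).

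| r (assumed) | 2(1−r) | 1−r² | Ratio | Variance cut | 78 × ratio | Power, change score | Power, adjusted |
|---|---|---|---|---|---|---|---|
| 0.3 | 1.40 | 0.91 | 0.65 | 35% | 50.7 | 45% | 63% |
| 0.5 | 1.00 | 0.75 | 0.75 | 25% | 58.5 | 59% | 71% |
| 0.7 | 0.60 | 0.51 | 0.85 | 15% | 66.3 | 80% | 86% |
| 0.8 | 0.40 | 0.36 | 0.90 | 10% | 70.2 | 93% | 95% |
| 0.9 | 0.20 | 0.19 | 0.95 | 5% | 74.1 | 99.8% | 99.9% |

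The column 78 × ratio is the number of participants with whom the adjusted analysis would match the change-score analysis of 78.

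**Check of the equivalence.** On one simulated data set of 78 clients with two occasions, the mixed-model interaction and the difference in mean change agreed: estimate 0.458, t = 2.23 for both. The standard error was 0.205 with free baseline means, 0.179 with a common baseline mean and 0.182 with the baseline as covariate.

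**If there were more occasions.** With 17 occasions and a linear slope, for r from 0.7 to 0.3, the cut is about 6% to 24% under compound symmetry, about 2% to 15% with an assumed random-slope variance of 0.3, and about 15% to 36% under a first-order autoregressive covariance.

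**The case against.** The strongest reply is that the quoted clause does not fix the model under criticism. A repeated-measures model with time and time-by-condition but no condition main effect is also a time-by-condition model, and with a suitable covariance it already gives the common-baseline analysis. The gain would then be nil. A journal article may leave that detail to an analysis plan, which is not shown here. This stands: a reader might infer that the plan ignores the baseline, but the text shows only that no use of it as an adjustment is stated.

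Second, a reader might infer that the planned estimate is biased. It is not. Under randomisation the interaction with free baseline means is unbiased, and the loss is one of precision only.

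Third, r may well be high. The framework describes the signature as stable across contexts, it is measured over six partners, and the SIP is repeated with the same ones. At r of 0.8 to 0.9 the cut is only 10% to 5% and power barely moves. This also stands, with a limit: stability is part of what Aim 2 tests. The framework further suggests that some people benefit from more synchrony and others from less, which could lower r under treatment. Moderate values cannot be ruled out.

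Fourth, the repeat SIP is placed at the end of treatment and is not expressly given to the waiting list at week 16. The flow charts, which might settle this, are not visible. A comparison of signature change between arms needs that measurement, so it is implied, but only implied.

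Finally, the primary outcome is the HRSD. This contrast concerns mechanism, and the signature consists of many features and not of one score.

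**Conclusion.** The point holds as a free efficiency improvement. The article does not say that the arm comparison of synchrony change uses the pre-randomisation SIP as a covariate or through a common baseline mean. Fitted conventionally to one SIP before and one after, the model is a change-score comparison. The variance of its arm contrast could then be cut by (1−r)/2, which is 5% at r = 0.9, 15% at r = 0.7 and 35% at r = 0.3. These percentages are shares of the contrast's own variance. All values of r are assumed, and the article's premise favours the smaller gains.

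The size rests on two SIP occasions in both arms, equal variances and a fitted condition main effect. The power figures rest further on 0.5 SD, 1:1 allocation and complete data, and are illustrations only. The documents do not support reading this as a flaw in validity, as a loss known to be large, or as a fault in the HRSD analysis.

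**What to change.** Add one sentence to the Study 2 statistical overview. Either of these would do:

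- Week-16 SIP synchrony is compared between arms with the baseline SIP value of the same client, and of the same partner, as a covariate.
- Time and time-by-condition are fitted without a condition main effect, so that the arms share one baseline mean, with an unstructured within-client covariance.

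The same sentence should say that the week-16 SIP is done in both arms. If the planned model already has the second form, it is enough to say so.

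The cost is one sentence of text. On the reading that the week-16 SIP is done in both arms, it needs no new data, visits or participants.
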